### Sample size calculation

The primary outcome variable is the prevalence of calculated blood loss >1000 mL or red blood cell transfusion in the intervention group (external aortic compression) compared with the control group (no aortic compression). Around 12.4% of elective CDs have gravimetrically diagnosed PPH >1000 mL.^24^ To demonstrate a clinically relevant relative risk reduction of 30% at 80% power, n=1069 women in each treatment arm are needed, assuming a significance level of α=0.05, two-sided test. The sample size is inflated by 5% to account for drop-out and heterogeneity between centres, resulting in a total sample size of n=2246 women. This sample size is also sufficient to detect relatively rare outcomes, such as intensive care or hysterectomy. Sample size calculations were performed by using the POWER procedure in SAS/STAT Software, V.9.4 of the SAS System for Windows (SAS Institute Inc., Cary, North Carolina, USA).

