**Trial registration number:**

NCT05312658.

STRENGTHS AND LIMITATIONS OF THIS STUDYMulticentre randomised controlled trial design.Blinded primary endpoint with severe postpartum haemorrhage, defined as calculated blood loss >1000 mL or blood transfusion.Powered to assess a 30% decrease in severe postpartum haemorrhage.Adheres to a recommended core outcome set for postpartum haemorrhage.Despite including 2246 patients, it is not powered to assess rare outcomes.

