### Randomisation

The randomisation sequence is generated electronically by the independent Karolinska Trial Alliance using random permuted blocks of varying sizes. The patients are randomised in a 1:1 ratio. The allocation is provided in opaque, sealed, numbered envelopes: either manual external aortic compression or no aortic compression (standard care). The surgeon or nurse opens the envelope in the operating room just before surgery and reads the allocation aloud. Due to the nature of the intervention, participants, surgeons and operating room staff cannot be blinded to treatment allocation. However, the primary endpoint is based on objective laboratory values and transfusion data entered into the eCRF and calculated after data extraction using a predefined formula. Outcome assessment and statistical analyses will therefore be performed blinded to treatment allocation.

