### Statistical analysis

Descriptive statistics will be used to characterise the groups recruited to the trial and to assess the comparability of the two groups at baseline. The primary efficacy analysis will be based on the intention-to-treat (ITT) population using a generalised linear mixed-effects model with log-link, Poisson distribution, treatment as a fixed effect and centre as a random effect to estimate the relative risk of event while accounting for centre effects. Similar methods will be employed for secondary and exploratory endpoints using appropriate models based on the type and distribution of the outcome. Patient-reported outcomes and questionnaire scales will be treated as numeric in this regard. Continuous variables will be adjusted for baseline values when applicable. All estimates will be provided with 95% CIs. Missing data exceeding 5% will be handled using multiple imputation.

The overall type-I error rate of the primary and five secondary endpoints will be retained at the 5% level using a hierarchical testing procedure. In case of a significant test for the primary endpoint, the entire probability mass will be transferred and distributed equally over the five secondary endpoints, that is, each receiving 1% of the total α=5%. The secondary endpoints will be tested sequentially, and the probability mass of a significant secondary outcome will be transferred (added) to the significance level for the next outcome in the order listed. All those significant tests will be considered confirmatory findings. Corrections for multiple testing of exploratory outcomes will be conducted using the Benjamini-Hochberg procedure, controlling the false discovery rate at the 5% level. Interaction analyses and subsequent subgroup analyses will be performed to assess treatment effects in subgroups and treatment effect heterogeneity based on having one or more risk factors for PPH with an OR of at least 3 in the literature: previous PPH, preeclampsia or multiple pregnancy.

Primary and secondary outcomes will also be presented for the per-protocol population. All safety outcomes will be presented for both the ITT population and the safety population (all randomised women according to actual treatment). The statistical analysis plan will be established in detail and signed before database lock and published as online supplemental material along with the main results.

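### The sample-size section says 2246 women suffice to detect intensive care or hysterectomy; the article's own limitations list says the opposite, and the arithmetic supports the limitations list.

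*Protocol article*

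**What the plan says.** The Sample size calculation section sizes the trial on one binary outcome. The control rate is taken from gravimetric data: "Around 12.4% of elective CDs have gravimetrically diagnosed PPH >1000 mL". The target is stated as "To demonstrate a clinically relevant relative risk reduction of 30% at 80% power, n=1069 women in each treatment arm are needed". The calculation uses a conventional two-sided test at the 5% level. The section then gives the total: "The sample size is inflated by 5% to account for drop-out and heterogeneity between centres, resulting in a total sample size of n=2246 women". Directly after this comes the sentence at issue: "This sample size is also sufficient to detect relatively rare outcomes, such as intensive care or hysterectomy". No control rate, effect or power accompanies it.

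The strengths and limitations list that follows the abstract says: "Despite including 2246 patients, it is not powered to assess rare outcomes".

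Under Secondary outcomes, transfer to intensive care appears only as a component of the fourth secondary endpoint, and hysterectomy only as a component of the fifth. Neither is a confirmatory endpoint on its own.

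**The concern.** Two statements in the current text assign opposite properties to the same 2246 women, so one of them is false. The sample-size sentence is the likelier error. A trial sized to just reach 80% power for a 30% reduction from 12.4% has no spare information for events that are much less frequent.

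The issue is how later results are interpreted. Severe maternal morbidity and safety are among the stated secondary objectives. If the sample-size section is taken at its word, a non-significant difference in intensive care or hysterectomy could be cited as evidence that compression has no effect on these events, or that it is safe. A handful of events per arm cannot support either conclusion.

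**Working it through.** **Inputs from the protocol article.** Control rate 12.4%, 30% relative reduction, 80% power, two-sided α = 0.05 and 5% inflation to 2246 (Sample size calculation); 1:1 allocation (Randomisation). Rates for intensive care and hysterectomy are not given. The rates of 0.1% to 1% used below are assumptions.

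**Step 1: reproduce the primary calculation.** With p1 = 0.124, p2 = 0.7 × 0.124 = 0.0868 and p̄ = 0.1054:

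n = [1.960·√(2p̄(1−p̄)) + 0.842·√(p1(1−p1) + p2(1−p2))]² / (p1−p2)² = 1068.4, rounded up to 1069 per arm.

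1069 × 1.05 = 1122.45, rounded up to 1123 per arm, and 2 × 1123 = 2246. Both stated figures reproduce exactly.

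**Step 2: how rare can an outcome be?** Fix n at 1123 per arm and solve the same formula for the control rate that gives 80% power at α = 0.05:

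| Relative reduction | Control rate needed |
|---|---|
| 30% (the planned effect) | about 11.9% |
| 50% | about 4.1% |
| 70% | about 1.8% |

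**Step 3: power at assumed rare rates.** The normal approximation is too generous at very low counts. These figures therefore sum exact binomial probabilities over the outcomes that the uncorrected chi-square test rejects (1123 per arm, two-sided 5%):

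| Assumed control rate | Expected control events | Power, halving | Power, 30% reduction |
|---|---|---|---|
| 0.1% | 1.1 | 1.7% | 1.5% |
| 0.5% | 5.6 | 14% | 7% |
| 1% | 11.2 | 28% | 12% |

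Fisher's exact test gives less: 20% for a halving and 8% for a 30% reduction, both at 1%.

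By the Step 1 formula, 80% power from a 1% control rate needs about 4,670 per arm for a halving and about 14,700 per arm for a 30% reduction.

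**Step 4: the most favourable case, complete elimination.** With no events under compression, Fisher's test needs at least 6 control events: 5 versus 0 gives p = 0.062 and 6 versus 0 gives p = 0.031. Power is then the probability that a Binomial(1123, p) count is at least 6:

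| True control rate | Power |
|---|---|
| 0.5% | 49% |
| 0.7% | 80% |
| 1% | 97% |

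Six events are an observed rate of 6/1123 = 0.53%. That is a count threshold, not a rate at which the trial has adequate power.

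**The case against.** **Every power figure for these events rests on assumed rates.** This is true, and a very large effect at the upper end of the range would be detectable: elimination from 1% has 97% power. A reader might infer that the claim fails under every conceivable effect, and the documents do not support that. What stands is that the article posits no such effect. For its own 30% reduction, any outcome below about 11.9% falls short of 80% power.

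**The wording might be read more mildly.** To detect could mean to observe at least one case, which has a probability of 1 − 0.999^2246 = 89% even at a 0.1% rate. But the sentence directly follows a power statement for a between-arm comparison and says the size is also sufficient. Separating relatively rare from rare does not help either, because hysterectomy is the named example.

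**The composites.** A reader might infer that the problem is worse for the fourth and fifth secondary endpoints, since the Statistical analysis section has the α "distributed equally over the five secondary endpoints, that is, each receiving 1% of the total α=5"%. The documents do not support this. Composite rates are not given, and they are at least as high as those of any component; the fourth endpoint also counts prolonged postoperative and hospital stays. The α of a significant secondary endpoint is passed on, so the fourth can be tested at up to 4% and the fifth at up to 5%. At an assumed 5% composite rate, power for a halving is about 71% even at α = 1%. The point is therefore confined to the individual events.

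**The harm is limited.** The limitations list already carries the right caveat, no passage says that a null result will be read as safety, and 95% CIs are promised for all estimates. This lowers the severity but does not remove the contradiction.

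**Conclusion.** The point holds for intensive care and hysterectomy as individual events. The contradiction needs no outside figure, and the article's own design inputs show which statement is wrong. Across assumed control rates of 0.1% to 1%, chi-square power is at most 28% for a halving and 12% for the planned 30% reduction.

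The Step 2 thresholds do not depend on the assumed rates; the power percentages do. All figures assume 1123 analysed women per arm and ignore drop-out and centre effects.

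Severity is moderate. A stated property of the design is false, but no endpoint, test or sample size depends on it, and the primary calculation is correct.

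**What to change.** Delete the sentence in the Sample size calculation section, or replace it with text that agrees with the limitations list. For example: the trial is not powered for intensive care or hysterectomy as individual events; they will be reported as counts by arm with 95% CIs; a non-significant difference will not be interpreted as absence of effect or as evidence of safety. Keep the limitation as it stands.

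If a detectable effect is quoted, give the true control rate for 80% power (about 0.7% under complete elimination, Fisher, two-sided 5%) and not the 0.53% observed-count threshold, at which power is only about 55%.

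The cost is wording only. The sample size, the endpoint hierarchy and the analysis are unchanged; one stated property of the design becomes less favourable.

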### Data statement

Data are entered by study personnel into an electronic case report form (eCRF) using REDCap,^25^ a secure web application for building and managing databases and online surveys, provided by Karolinska Institutet. Data are handled in accordance with the General Data Protection Regulation and protected from unauthorised access through digital security solutions provided by Karolinska Institutet. Questionnaires are set up and distributed through REDCap. Data from the Swedish Pregnancy Register, the Swedish Neonatal Quality Register and the Patient Register will be extracted based on unique personal identification numbers and added to the database.

### Statistical analysis

Descriptive statistics will be used to characterise the groups recruited to the trial and to assess the comparability of the two groups at baseline. The primary efficacy analysis will be based on the intention-to-treat (ITT) population using a generalised linear mixed-effects model with log-link, Poisson distribution, treatment as a fixed effect and centre as a random effect to estimate the relative risk of event while accounting for centre effects. Similar methods will be employed for secondary and exploratory endpoints using appropriate models based on the type and distribution of the outcome. Patient-reported outcomes and questionnaire scales will be treated as numeric in this regard. Continuous variables will be adjusted for baseline values when applicable. All estimates will be provided with 95% CIs. Missing data exceeding 5% will be handled using multiple imputation.

The overall type-I error rate of the primary and five secondary endpoints will be retained at the 5% level using a hierarchical testing procedure. In case of a significant test for the primary endpoint, the entire probability mass will be transferred and distributed equally over the five secondary endpoints, that is, each receiving 1% of the total α=5%. The secondary endpoints will be tested sequentially, and the probability mass of a significant secondary outcome will be transferred (added) to the significance level for the next outcome in the order listed. All those significant tests will be considered confirmatory findings. Corrections for multiple testing of exploratory outcomes will be conducted using the Benjamini-Hochberg procedure, controlling the false discovery rate at the 5% level. Interaction analyses and subsequent subgroup analyses will be performed to assess treatment effects in subgroups and treatment effect heterogeneity based on having one or more risk factors for PPH with an OR of at least 3 in the literature: previous PPH, preeclampsia or multiple pregnancy.

Primary and secondary outcomes will also be presented for the per-protocol population. All safety outcomes will be presented for both the ITT population and the safety population (all randomised women according to actual treatment). The statistical analysis plan will be established in detail and signed before database lock and published as online supplemental material along with the main results.

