#### Primary outcome

The prevalence of severe PPH, defined as a calculated estimated blood loss greater than 1000 mL or a red blood cell transfusion within 48 hours after delivery, will be compared between the groups. The calculated estimated blood loss = the estimated blood volume × (preoperative EVF − postoperative EVF) ÷ preoperative EVF. The estimated blood volume in millilitres is calculated as the preoperative body weight in kilograms × 85.^10^

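### The primary analysis gives a binary outcome a Poisson likelihood and names no variance correction; if fitted with model-based standard errors, it has about 3 points less power than the test used for the sample size

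*Protocol article*

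**What the plan says.** The primary outcome is binary: severe postpartum haemorrhage, "defined as a calculated estimated blood loss greater than 1000 mL or a red blood cell transfusion within 48 hours after delivery" (Primary outcome). The Statistical analysis section fixes the model as a "generalised linear mixed-effects model with log-link, Poisson distribution, treatment as a fixed effect and centre as a random effect to estimate the relative risk". It gives the distribution, the link, the fixed effect and the random effect. It mentions no sandwich variance, dispersion parameter or binomial likelihood, and it does not say that model-based standard errors will be used. Details are left to a statistical analysis plan to be signed before database lock. For other outcomes the section adds: "Similar methods will be employed for secondary and exploratory endpoints using appropriate models based on the type and distribution of the outcome".

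The Sample size calculation section starts from this rate: "Around 12.4% of elective CDs have gravimetrically diagnosed PPH >1000 mL". It continues: "To demonstrate a clinically relevant relative risk reduction of 30% at 80% power, n=1069 women in each treatment arm are needed". The test there is two-sided at the 5% level. The section then adds a margin: "The sample size is inflated by 5% to account for drop-out and heterogeneity between centres, resulting in a total sample size of n=2246 women".

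**The concern.** A Poisson variable with mean p has variance p. A yes/no variable has variance p(1−p), which is smaller. A Poisson model fitted to binary data still estimates the relative risk properly, but its ordinary standard errors are too large by a factor of about 1/√(1−p). The random centre intercept is no remedy: it can add variance between centres, but it cannot take away excess variance assumed within them.

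The sample size appears to rest on the smaller, binomial variance. If the analysis used the larger one, the powered test and the planned test would differ. The intervals would then be too wide and the 5% test too strict, and the trial would have less power than stated. Binary secondary endpoints analysed in the same way would share the problem. They start at a 1% level, and non-significance there also stops the level passing to the next endpoint.

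**Working it through.** **Inputs.** From Sample size calculation: control rate 12.4%, relative risk 0.70 (so 8.68% under intervention), two-sided α 0.05, 80% power, 1069 per arm, 5% inflation. From Randomisation: 1:1 allocation. The number of centres, 10, is from the abstract.

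**1. Reproduce the plan's figure.** For the two-proportion test with pooled variance and mean rate 0.1054:

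n = [1.960·√(2·0.1054·0.8946) + 0.8416·√(0.124·0.876 + 0.0868·0.9132)]² / 0.0372²
= (0.8511 + 0.3648)² / 0.001384 = 1068.4, so 1069 per arm.

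Then 1069 × 1.05 = 1122.45, so 1123 per arm and 2246 in total. Both figures reproduce, and the calculation uses binomial variance.

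**2. Standard error of the log relative risk at 1069 per arm.**

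- Poisson, model-based: √(1/(1069·0.124) + 1/(1069·0.0868)) = √(0.007544 + 0.010777) = 0.1354.
- Binomial: √(0.018321 − 2/1069) = √0.016450 = 0.1283.
- Ratio: 1.055.

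**3. Power.** The estimate varies with the binomial standard error but is judged against the Poisson one: Φ((|log RR| − 1.96·SE_Poisson)/SE_binomial), with |log 0.70| = 0.3567.

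- 1069 per arm: (0.3567 − 0.2653)/0.1283 = 0.712, so 76.2%.
- 1123 per arm: standard errors 0.1321 and 0.1251, so 78.3%.

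One million simulated trials per setting, without centre effects, give:

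| Evaluable per arm | Poisson SE, formula | Poisson SE, simulation | Valid SE, formula | Valid SE, simulation |
|---|---|---|---|---|
| 1069 | 76.2% | 76.7% | 79.4% | 80.0% |
| 1123 | 78.3% | 78.8% | 81.3% | 81.9% |

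Like for like, the loss is about 3 points. A likelihood-ratio test in the Poisson model does not avoid it (77.0% and 79.1%). With uncorrected standard errors, about 1171 evaluable women per arm would be needed for 80%.

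**4. Type I error.** The formula is 2·(1 − Φ(1.96/√(1−p))). It gives 3.6% at p = 12.4% and 3.8% at p = 10.54%. Simulation gives 3.5% and 3.8%. A valid variance gives about 4.9%.

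**5. Centre variation.** This used 10 equal centres with balanced arms, 100,000 trials per setting, and an assumed centre SD on the log scale of 0, 0.3 and 0.5. Power with the Poisson standard error is 76.1–76.8% at 1069 and 78.2–78.9% at 1123. Type I error is 3.3–3.7%.

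**6. Other control rates** (assumed except 13%, which the Introduction gives for Sweden in 2024), at relative risk 0.70 and 1069 per arm, by formula:

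| Control rate | SE too large by | Power, Poisson SE | Power, valid SE |
|---|---|---|---|
| 8% | 3.5% | 56.4% | 59.1% |
| 10% | 4.4% | 66.4% | 69.5% |
| 13% | 5.8% | 78.3% | 81.5% |
| 20% | 9.4% | 93.5% | 95.6% |

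**7. Binary secondary endpoints.** The article gives no rates for them, so these are assumed. The excess in the standard error, 1/√(1−p) − 1, is 0.5% at a prevalence of 1%, 1.5% at 3%, 5.4% at 10%, 11.8% at 20% and 19.5% at 30%. A nominal 1% test would run at about 0.7%, 0.4% and 0.2% at the last three.

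**The case against.** The strongest reply is that the missing correction is read from silence. The article names no variance estimator of either kind, and it defers detail to an analysis plan and a full protocol that are not shown. A robust variance there would remove the loss. This stands, and it makes the finding conditional. It does not dispose of it, because the article does fix the likelihood, and ordinary fitting of that likelihood gives model-based standard errors that do not match the sample size.

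Second, 2246 women are to be enrolled. If all are evaluable, power is 78–79%, within 2 points of the target. This also stands. However, the 5% margin is already assigned to drop-out and centre heterogeneity, and once it is used up the figure returns to about 76%.

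Third, the effect is no larger than the uncertainty in the control rate. At 13%, uncorrected power would be 80.3% at 1123 per arm. That is true, but a higher rate raises power under either variance and leaves a gap of about 3 points. Neither rate is shown to apply to calculated blood loss.

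Fourth, the error is conservative, and secondary endpoints are to have models suited to their type, so Poisson is not fixed for each of them. Both points are accepted.

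A reader might infer that the trial simply has 76% power, or that a positive result would be unreliable. The documents support neither. The first needs both model-based standard errors and only 1069 evaluable per arm. The second has the direction of the error wrong.

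**Conclusion.** The point holds in conditional form. The stated likelihood does not suit a binary outcome unless its variance is corrected, and the stated 80% rests on binomial variance. With model-based Poisson standard errors at 12.4% versus 8.68%, the standard error is about 5.5% too large and the 5% test runs at about 3.5–3.8%. Power is about 76% at 1069 evaluable per arm and 78–79% at 1123. The relative risk estimate is not biased and false positives are not increased; the harm is lost precision and some lost power. For other binary endpoints analysed in the same way, the effect is negligible when events are rare and grows with prevalence. Its size for any particular secondary endpoint cannot be stated from the article.

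**What to change.** Before the statistical analysis plan is signed, keep the relative risk and name a valid variance for all binary endpoints. Either option works:

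- log-link Poisson with participant-level robust (sandwich) standard errors and centre as a fixed effect; or
- a logistic model with centre, reporting a standardised relative risk with a delta-method or bootstrap interval.

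A sandwich clustered on centre should be avoided, because 10 centres are too few for it to be reliable.

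The change takes a short passage in the plan and the matching code, with no extra data or participants. The price is a change to the stated model: centre moves from a random to a fixed effect, or the model family changes. If the model-based Poisson analysis is kept, the power should be restated as about 76% at 1069 evaluable per arm (about 78% at 1123).

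### The primary model adjusts for centre only; prespecified baseline adjustment with a standardised, robust relative risk would add modest precision to an already valid analysis

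*Protocol article*

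**What the plan says.** In the protocol article, Statistical analysis, the primary intention-to-treat analysis is a generalised linear mixed model with log link and Poisson distribution, with "treatment as a fixed effect and centre as a random effect to estimate the relative risk of event while accounting for centre effects". No other covariate is named. The only baseline-adjustment rule is "Continuous variables will be adjusted for baseline values when applicable", which does not reach a binary endpoint.

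Under Primary outcome, severe PPH is a calculated loss above 1000 mL or a red-cell transfusion within 48 hours. Calculated loss is blood volume times the relative fall in EVF: "The estimated blood volume in millilitres is calculated as the preoperative body weight in kilograms" times 85. Under Enrolment, weight is taken at most 4 days and blood samples at most 7 days before surgery, and randomisation follows in the operating room.

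The same Statistical analysis section chooses "previous PPH, preeclampsia or multiple pregnancy" for the subgroup and interaction analyses because each is reported to carry an odds ratio of at least 3. They are given no other role. The detailed SAP is still to be signed before database lock.

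Sample size calculation: "To demonstrate a clinically relevant relative risk reduction of 30% at 80% power, n=1069 women in each treatment arm are needed", then "The sample size is inflated by 5% to account for drop-out and heterogeneity between centres, resulting in a total sample size of n=2246 women".

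**The concern.** The plan accepts baseline adjustment in principle but does not apply it to the endpoint that carries the confirmatory claim. By the plan's own account, three factors are strongly prognostic for PPH. Two further baseline values, weight and preoperative EVF, are inputs to the endpoint and may be prognostic. All of these data are needed anyway, for the endpoint or for the subgroups.

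What is at stake is precision. Adjustment for prognostic baseline variables can narrow the confidence interval for the relative risk at no cost in patients. The type I error and the validity of the planned comparison are not in question. Because the article states the primary model completely, centre-only adjustment is a stated choice and not merely a detail left open.

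**Working it through.** **Inputs from the protocol.** Control risk 12.4% ("Around 12.4% of elective CDs have gravimetrically diagnosed PPH >1000 mL"); 30% relative reduction, so treated risk 0.124 × 0.70 = 8.68%; "assuming a significance level of α=0.05, two-sided test"; 80% power; 1:1 allocation. The documents do not say how much outcome variance the baseline data explain (R²), so every R² below is an assumption shown as a range.

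**Step 1: the plan's own figure.** Two proportions, pooled variance under the null, no continuity correction:

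n = [1.960 √(2 × 0.1054 × 0.8946) + 0.8416 √(0.124 × 0.876 + 0.0868 × 0.9132)]² / 0.0372² = 1068.4, so 1069 per arm. Power at 1069 is 80.0%. Then 1069 × 1.05 rounds up to 1123 per arm, 2246 in total. Both figures match.

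On the log relative risk scale at 1069 per arm, SE = √(0.876/(1069 × 0.124) + 0.9132/(1069 × 0.0868)) = 0.128, which gives 79.4% power. The centre-only analysis therefore delivers what was planned, before any loss from centre heterogeneity.

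**Step 2: gain for a given R².** Approximate effective size per arm is n/(1 − R²).

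| R² (assumed) | Power at 1069 per arm | n per arm for 80% | Power at 1123 per arm |
|---|---|---|---|
| 0 | 80.0% | 1069 | 81.9% |
| 0.02 | 80.8% | 1048 | 82.7% |
| 0.05 | 82.0% | 1016 | 83.8% |
| 0.08 | 83.2% | 984 | 85.0% |
| 0.10 | 84.0% | 963 | 85.7% |

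**Step 3: the risk-factor flag.** For a binary factor with prevalence π and risks p₀ (absent) and p₁ (present) averaging 12.4%, R² = π(1 − π)(p₁ − p₀)² / (0.124 × 0.876). With odds ratio 3 and π = 0.10, p₀ = 0.1081 and p₁ = 0.2667, so R² = 0.021. Over an assumed π of 5 to 20%, R² is 0.012 to 0.031, or about 0.5 to 1.2 power points. With an assumed odds ratio of 5, R² is 0.033 to 0.073, or about 1.3 to 3 points.

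**Step 4: weight and EVF.** The relative EVF fall needed to exceed 1000 mL is 1000/(85 × weight): 19.6% at 60 kg, 13.8% at 85 kg and 10.7% at 110 kg. These thresholds do not by themselves show prognostic value. I assumed a weight coefficient of variation of 17%, a correlation of preoperative EVF with loss of 0 to 0.3, and two loss distributions (mean 500, SD 420 mL; mean 350, SD 560 mL).

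- Loss in mL unrelated to weight, EVF not prognostic: R² = 0.
- Relative EVF fall unrelated to weight, EVF not prognostic: R² = 0.030 to 0.048.
- Both effects at their most favourable: R² = 0.086, power 83.4%.

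The highest values from Steps 3 (at odds ratio 3) and 4 sum to 0.117, but they need not occur together. I use 0.10 as the upper end.

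**Step 5: does the stated model deliver the gain?** Simulated Poisson log-link fits, 1069 per arm, 1500 replicates, no centre effect, one covariate with R² of 0.069 in controls:

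| Method | Mean SE of log RR | Power |
|---|---|---|
| Unadjusted, model-based SE | 0.1362 | 77.7% |
| Adjusted, model-based SE | 0.1362 | 78.7% |
| Unadjusted, robust SE | 0.1291 | 81.0% |
| Adjusted, robust SE | 0.1254 | 83.5% |
| Standardised from a logistic model | 0.1251 | 83.5% |

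Model-based Poisson variance overstates the variance of a binary outcome, and covariates leave it unchanged. With robust variance, adjustment cuts the variance by 1 − (0.1254/0.1291)² = 5.6% and adds 2.5 power points.

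**The case against.** The strongest reply is that nothing here is wrong. A treatment-plus-centre analysis of a randomised comparison is valid, it matches the unadjusted sample-size calculation, and that calculation reproduces. Covariate sets are often settled in the SAP, which is not shown. The gain is small and rests on inputs that the documents do not give. All of this stands, and it limits the point to a recommendation.

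It does not remove the point. The article states the primary model in full and confines baseline adjustment to continuous variables, so an SAP that follows it would leave the covariates out. For the risk factors, prognostic strength is the plan's own premise.

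A reader might go further in four ways that the documents do not support:

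- *Weight must be prognostic because it is in the formula.* It need not be. If the volume lost does not depend on weight, the EVF fall shrinks as blood volume grows, and weight predicts nothing.
- *Chance imbalance in weight threatens the result.* With an assumed SD of 15 kg and 1069 per arm, the SE of the mean difference is 15 × √(2/1069) = 0.65 kg, so 95% of randomisations fall within about ±1.3 kg. The unadjusted confidence interval already allows for this.
- *The trial lacks power without covariates.* It reaches its stated 80% at 1069 per arm, and 5% is added for drop-out and heterogeneity between centres.
- *Adding covariates to the stated model is enough.* With model-based standard errors it gains essentially nothing (Step 5).

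**Conclusion.** The point holds as an efficiency improvement. The primary analysis forgoes modest precision that data already collected could supply. It is not an error or a contradiction, and it gives no reason to doubt the planned test or the sample size.

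The expected gain is about 0 to 4 power points at 1069 per arm, for an assumed R² of 0 to 0.10. This is equivalent to needing up to 106 fewer women per arm (1069 − 963). The most dependable part is the risk-factor flag, at about 0.5 to 1.2 points. That rests on the protocol's minimum odds ratio of 3 carrying over to the calculated-loss endpoint and on an assumed prevalence of 5 to 20%. The contribution of weight and EVF ranges from nothing to an R² of 0.086, and the documents cannot settle where in that range it lies. Any gain depends on a robust or standardised estimator.

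**What to change.** Before the SAP is signed, prespecify a primary model that adds three terms to centre: a flag for "previous PPH, preeclampsia or multiple pregnancy", preoperative weight and preoperative EVF. Define the flag only from information known before randomisation. Report a standardised (marginal) relative risk with a robust confidence interval, and name the variance method. Keep the centre-only model as a prespecified sensitivity analysis. State in the SAP that this departs from the model in the published Statistical analysis section, so that the two can be reconciled.

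The cost is a short SAP entry and no new data, since weight and EVF are required for the endpoint and the risk factors for the subgroups. The downside is a slightly more complex estimator that differs from the published model.
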